##### Parents’ endpoints

Anxiety: The Spielberger state-trait anxiety inventory (STAI) will be used to assess anxiety. The STAI is a self-reporting questionnaire consisting of 40 items that measure both the state and trait scores. These scores range from 20 (absence of anxiety) to 80 (high anxiety) [60]. This questionnaire will assess if anxiety is impacted as a result of parental intervention (mother).

##### Rationale for the secondary endpoints

It is of value to measure the impact of intervention on the WM and on other non-trained brain processes as well as on parental anxiety, child behavior and parental perceptions of the child’s quality of life.

### Participant timeline

The total participation time is 20 months (Fig. 1).

**Fig. 1 Fig1:**
[figure not shown]
Flowchart EPIREMED Study

### Sample size

The sample size was calculated to obtain an 80% power to detect a difference of 7.5 points on the VSI index (estimated standard deviation: 15) at 18 months (+/− 2 months) between the two groups. This has been considered to be clinically significant considering other similar studies [5]. With the threshold for statistical significance set at a *p*-value of 0.05, assuming that a potential 15% of patients will be lost to follow-up between baseline and last assessments, these calculations showed that 166 patients are needed (83 per group [Power Analysis and Sample Size Software Version 2008, Utah, USA]). Assuming that 30–40% of the EPIPAGE 2 children will present with a WM abnormality, 1600 children will be required for screening.

### Recruitment

The study will include children in EPIPAGE 2 from the regions participating in the present study (EPIREMED). Recruitment will be at the end of the EPIPAGE 2 assessment (5 ½ years). The EPIPAGE 2 protocol and the main perinatal results are described in two publications of Ancel P-Y et al. [2, 61].

The EPIPAGE 2 clinical research coordinator will establish a monthly, per center list of potentially eligible patients to EPIREMED. Using this list, each center’s referring staff person will organize the first telephone interface with those qualified families having a WM index lower than 85, who have no exclusion criteria and who have the ability to travel to the testing centers.

Thereafter, the coordinator will contact those families to further coordinate their EPIREMED participation. The coordinator will explain the study’s objectives, its development, and its advantages and disadvantages.

Those families accepting to participate will receive a parent information letter describing all topics discussed by telephone, an information text specifically adapted for a child, an informed consent and a verification of their appointment. Travel expenses will be reimbursed.

### Randomization

A randomization list will be established before the implementation of the study with a 1:1 allocation ratio, and will be elaborated by a secure Clinical Research Platform. A computer-generated, randomized list using a permuted block design will be done (stratified on center and gemellarity: singleton/twin). Multiple births represent 30% of the preterm population within the EPIPAGE 2 group. If one twin has a WM anomaly, this child will be selected for randomization.

### Data collection methods

#### The inclusion visit

After consents have been obtained from the parent or legal guardian, the following assessment will be obtained:
The children
Assessment of the working memory index (WMI)Auditory attention, statue, and design fluency of the NEPSY-2Language and verbal skills (CLéA)

This assessment will be made by a neuropsychologist and will last about 90 minutes.
b)The parents:
A self-administered questionnaire on anxiety (STAI)A questionnaire assessing the behavior of the child (Goodman)A questionnaire assessing the child’s QoL (VSP-A)c)The teachers:
A questionnaire assessing the School Adaptation (GSA questionnaire)

The Cogmed JM group will begin no later than 2 months after the participants’ inclusion and the standard group will receive routine management. A similar follow up will be planned for the two groups, based on their intermediate and final visits.

#### The 8 month (+/− 2 months) intermediate visit

An assessment will be conducted 8 months (+/− 2 months) after the participants are included in the study and will consist of:
The children
Assessment of the working memory index (WMI)IQ and its main indices (WPSSI IV)Auditory attention, statue, and design fluency of the NEPSY-2Language and verbal skills (CLéA)

This assessment will be made by a neuropsychologist and will last about 180 minutes.
b)The parents:
A self-administered questionnaire on anxiety (STAI)A questionnaire assessing the behavior of the child (Goodman)A questionnaire assessing the child’s QoL (VSP-A)c)The teachers:
A questionnaire assessing the School Adaptation (GSA questionnaire)

#### The 18 month (+/− 2 months) final visit

Children in both the intervention and control groups will receive a final 18-month evaluation (+/− 2 months) after inclusion; they will then be between 7 and 7½ years old.

The primary evaluation end point: The visuospatial index and the working memory index of the WPPSI-IV will be used for this visit. The WMI will be used to determine the long-term maintenance of the working memory and its impact on intelligence. Auditory attention of NEPSY-2 will be used in this final evaluation. A neuropsychologist will make the assessment that will last about 30 min.

### Data management

Using EpiData software, a specific database will be created. Each participant will be assigned a unique, anonymous number and a data quality control will be performed by a physician to minimize any data inconsistencies.

### Statistical methods

Data will be analyzed using the Statistical Package for the Social Sciences (SPSS) version 20.0 software. Statistical significance is defined as *p* < 0.05. The methodology will be based on the Consolidated Standards of Reporting Trials Statement (CONSORT, http:// www.consort-statement.org/consort-statement/) [62].

The full analysis set will be used for the primary analysis. There is no interim analysis planned.

Demographic and baseline characteristics will be summarized. Quantitative data will be shown as mean ± standard deviation or median with its interquartile range. The qualitative data will be described as percentages with a 95% confidence interval.

#### Analysis of primary endpoint

The mean scores of the VSI will be compared between groups (Student t test or Mann Whitney test). Linear regression will be performed to adjust for potential confounding factors; variables relevant to the models will be selected on their clinical interest and/or a threshold *p*-value <= 0.1 during bivariate analysis. The final models will express the beta standardized. The unadjusted analysis will be the primary analysis, and the adjusted analysis will be secondary analysis.

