## Methods/design

### Study design

This study is designed as a multicenter (18 units of French university hospitals), randomized, controlled, open-label, two-parallel groups study. The recruitment will be prospective. The two groups are:
A control group: standard care management,an experimental group: standard care management in association with a 2-month Cognitive Training program called Cogmed JM.

The list of the recruiting centers is availed in website *clinicaltrial.gov*

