### Endpoints

#### Primary endpoint

The visual-spatial processing will be assessed by using the visuospatial index (VSI) of the WPPSI-IV at the inclusion visit, the six-month post-inclusion (+/− 2 months) and at 18-months post inclusion (+/− 2 months). This index consists of two subtests: block design and object assembly. The average score is 100 with a standard deviation of 15.

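### The primary analysis is an unadjusted t or Mann-Whitney test that leaves out baseline VSI and the randomisation strata: valid, but less precise than it need be, with an adjusted model that is not fixed in advance

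*Protocol article*

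**What the plan says.** All references are to the protocol article.

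- **Primary test.** Analysis of primary endpoint: "The mean scores of the VSI will be compared between groups (Student t test or Mann Whitney test". No rule decides between the two tests.
- **Ranking.** The same section: "The unadjusted analysis will be the primary analysis, and the adjusted analysis will be secondary analysis".
- **Adjusted model.** A linear regression whose covariates "will be selected on their clinical interest and/or a threshold" of p at or below 0.1 in bivariate analysis. The result is to be given as a standardised beta. Baseline VSI, centre and twin status are not named as covariates.
- **Strata.** Randomization: "stratified on center and gemellarity: singleton/twin". Study design: "multicenter (18 units of French university hospitals".
- **Baseline VSI.** Primary endpoint says that visuospatial processing is "assessed by using the visuospatial index (VSI) of the WPPSI-IV at the inclusion visit" and again at the two follow-up times. Children's endpoints says that the main WPPSI-IV indices, which include the visual spatial index, are measured in EPIPAGE 2 follow-up. The list under The inclusion visit, however, begins "Assessment of the working memory index (WMI)Auditory attention, statue, and design fluency of the NEPSY-2Language" and contains no VSI.
- **Other use of baseline.** Analysis of secondary endpoints plans a repeated-measures comparison over baseline, 8 and 18 months. It stands under the secondary endpoints and does not change the primary analysis.

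**The concern.** The outcome is an index that, according to the article, is also measured in the same child before training. A baseline value of the outcome is usually the most useful covariate a trial has. Leaving it out keeps chance baseline imbalance in the estimate and gives a wider interval than necessary, though one with correct coverage.

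Leaving out the strata has a different effect. Stratified allocation balances centre and twin status between arms, but the t test's standard error still counts the variation they explain. The interval is then too wide for its nominal 95%, and the test rejects less often than 5% under the null.

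Two further choices are left open. The Mann-Whitney test does not estimate the mean difference on which the sample size is based. In the adjusted model, the and/or wording lets the p-value screen decide alone, so the model could omit baseline VSI and both strata. A standardised beta also cannot be read directly against the planned 7.5 points.

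**Working it through.** **Inputs from Sample size and Randomization:** difference 7.5 points, SD 15, alpha 0.05 (taken as two-sided), power 80%, 15% loss, 1:1 allocation, 166 children (83 per group).

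**Assumption:** correlation r between baseline and 18-month VSI of 0.3 to 0.7. The article gives no value.

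**The plan's own figure.** n per arm = 2(1.96 + 0.84)² × 15² / 7.5² ≈ 63 (64 with the exact t). Divided by 0.85 this is 75 (76), or 150 (152) in total. The stated 166 is larger and is not reproduced. That is a separate matter; it means only that the trial has some margin. Evaluable children: 166 × 0.85 ≈ 141, or about 70 per arm.

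**Baseline adjustment.** The residual SD is 15√(1 − r²). Power is from the exact t at 70 per arm. The 95% half-width is 1.96 × SD × √(2/70). Total N is for 80% power with 15% loss.

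| r | Residual SD | Power for 7.5 points | Half-width (points) | Total N |
|---|---|---|---|---|
| none (unadjusted) | 15.00 | 83.6% | 4.97 | 152 |
| 0.3 | 14.31 | 86.8% | 4.74 | 140 |
| 0.4 | 13.75 | 89.3% | 4.55 | 128 |
| 0.5 | 12.99 | 92.4% | 4.30 | 116 |
| 0.6 | 12.00 | 95.7% | 3.98 | 100 |
| 0.7 | 10.71 | 98.4% | 3.55 | 80 |

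The variance falls by r², that is by 9% at r = 0.3 and 49% at r = 0.7.

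**Strata.** If centre and twin status explain a share R² of the VSI variance (also not given), the true size of the unadjusted test is about 2[1 − Φ(1.96/√(1 − R²))]. Without adjustment, power is Φ[(2.958 − 1.96)/√(1 − R²)]. With adjustment it is Φ[2.958/√(1 − R²) − 1.96]. Here 2.958 = 7.5/(15√(2/70)). These are normal approximations.

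| R² | True size, unadjusted | Power, unadjusted | Power, adjusted |
|---|---|---|---|
| 5% | 0.044 | 84.7% | 85.9% |
| 10% | 0.039 | 85.4% | 87.7% |
| 20% | 0.028 | 86.8% | 91.1% |

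**Covariate screening.** A simulation used 70 per arm, 15 candidate covariates of which one had r = 0.5, entry at p ≤ 0.1, and 4,000 runs. Type I error was 0.050 with screening and 0.050 with a pre-specified ANCOVA. Power was 91.9% and 92.4%. In this setting the screen cost almost nothing in error rate.

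**The case against.** The strongest reply is that nothing here is invalid. The unadjusted difference is unbiased under randomisation, its primary status is fixed in advance, and it matches a sample size built on the marginal SD of 15. At 70 per arm it has 83.6% power, above the 80% target. All of this stands, so the point concerns efficiency.

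The size of the gain is also uncertain. The correlation is assumed, and selecting children on IQ and working memory index could lower it. The figures are for complete cases, whereas the section on missing data counts children without the endpoint as failures. If values are assigned to them, neither 70 per arm nor the assumed SD and correlation applies, and the gain would probably shrink. This stands as a limit on the figures.

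A condensed article may leave a covariate list or the handling of centres to an analysis plan that is not shown. That is fair for details, but the unadjusted primary analysis, the open choice of test, the p ≤ 0.1 screen and the standardised beta are all stated here.

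Three stronger readings are tempting:

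- **Screening spoils the error rate of the adjusted model.** The simulation does not show this. The text also allows selection on clinical interest, so the data need not decide. The harm is a model left open to choice.
- **Baseline VSI already exists for every child.** The inclusion criteria name only total IQ and the working memory index, and the inclusion-visit list has no VSI. Children's endpoints supports the claim only in general terms.
- **The trial is underpowered because of this choice.** On its own inputs it is not.

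**Conclusion.** The point holds as an avoidable loss of precision and an incomplete specification. The primary analysis as stated is unbiased and, because it ignores the strata, somewhat conservative. For r between 0.3 and 0.7, adjusting for baseline would raise power from about 84% to between 87% and 98%. It would cut the half-width from 5.0 to between 4.7 and 3.5 points. These figures rest on an assumed correlation, SD 15 and 70 complete cases per arm, but the direction holds for any appreciable correlation. Separately, the choice between the t and Mann-Whitney tests has no rule, the adjusted model may leave out the covariates that matter most, and its reported coefficient is not on the scale of the planned effect. The change should be made, but results from the present plan would not be invalid without it.

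**What to change.** 1. Make the primary analysis one pre-specified ANCOVA of 18-month VSI on arm, baseline VSI, twin status and centre. With 18 × 2 = 36 possible strata for about 141 evaluable children, fit centre as a random effect or pool small centres by a rule set in advance.
2. Report the adjusted mean difference in VSI points with its 95% confidence interval. Keep the unadjusted t test as a sensitivity analysis.
3. Remove the p ≤ 0.1 screen, the standardised beta and the open Mann-Whitney alternative.
4. Reconcile the Primary endpoint section with The inclusion visit on whether baseline VSI comes from the inclusion visit or from the EPIPAGE 2 five-year WPPSI-IV, and name that source as the covariate.

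The cost is wording, agreed before outcomes are analysed, provided that a baseline VSI is held for the randomised children. Step 4 has to confirm that first.

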##### Methodology to account for missing data

Children not meeting the primary endpoint measurements will be considered as having failed in the study regardless of their randomization group. Additional analyses will be conducted based on:
Available data and,After multiple imputation of missing data.

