#### Exclusion criteria

Children and / or parents wishing to interrupt his / her participation during the study.

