##### Patient selection to include in the analysis

All the children registered and randomized in the study will be included in the analysis, respecting the intention to treat. This analysis will be conducted, if necessary, under the maximum bias hypothesis. In a second step, those wrongly included, and any major protocol deviations, will be excluded from the analysis.

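### A missing primary outcome is counted as a failure, but the primary analysis compares mean VSI scores and the plan gives failure no score, rank or cut-off

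*Protocol article*

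**What the plan says.** The section on the primary endpoint makes the outcome a continuous index: "The visual-spatial processing will be assessed by using the visuospatial index (VSI) of the WPPSI-IV", with 18 months as the time point of the primary objective. It describes the scale thus: "The average score is 100 with a standard deviation of 15".

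The section on analysis of the primary endpoint says "The mean scores of the VSI will be compared between groups (Student t test or Mann Whitney test"), and then "The unadjusted analysis will be the primary analysis, and the adjusted analysis will be secondary analysis".

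Under the heading on missing data, the rule is "Children not meeting the primary endpoint measurements will be considered as having failed in the study regardless of their randomization group". The next sentence opens "Additional analyses will be conducted based on" and lists two approaches: available data, and multiple imputation. By that ordering, the failure rule governs the primary analysis.

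The section on patient selection keeps all randomized children in the analysis by intention to treat and adds: "This analysis will be conducted, if necessary, under the maximum bias hypothesis". It gives no trigger, no definition and no values.

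**The concern.** Counting a missing child as a failure is well defined when the endpoint is success or failure. Here the endpoint is a score and the comparison is of group means. The article sets no responder threshold on the VSI, and no value or rank for a child who has failed. Whoever runs the primary t test must therefore pick a number.

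This is not a detail that the article leaves to an analysis plan. The article does fix the handling of missing data, and fixes it in a form that does not fit its own primary analysis. An analysis plan could carry out the rule only by supplying a score or rank, or else by departing from the protocol.

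The sample size section itself expects 15% loss, so about 12 of 83 children per arm would enter the primary analysis with an assigned value. The trial is open-label. A value chosen after data have accrued would leave room to influence the main result.

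**Working it through.** **Inputs from the protocol (sample size section).** Difference 7.5, SD 15, 80% power, alpha 0.05, 15% loss, 83 per arm. A two-sided test is assumed because the protocol does not state the sides.

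**The plan's own figure.** n = 2(1.96 + 0.84)² × 15² / 7.5² = 63 per arm (64 by the exact t test). Dividing by 0.85 gives 75 (76) per arm, or 150 to 152 in total. The stated 166 is larger than its inputs require. That does not affect this point.

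**Reference: available cases.** 83 × 0.85 = 70.55 per arm. z = 7.5 / (15 × √(2/70.55)) = 2.97, so power = Φ(2.97 − 1.96) = 84%.

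**Assumptions, not in the documents.** Control mean 90; loss unrelated to the score; a failed child receives a score v, tried from 45 to 80.

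**Formulas.** For an arm with observed mean m and missing share p:
- mean = (1 − p)m + pv
- variance = (1 − p) × 225 + p(1 − p)(m − v)²
- SE of the difference = √((variance in training + variance in control) / 83), with a normal approximation for power.

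**Equal loss, 15% per arm, true difference 7.5.** The expected difference is 0.85 × 7.5 = 6.375 for any v, because the assigned scores cancel.
- v = 45: variances 191.25 + 0.1275 × 52.5² = 542.7 and 191.25 + 0.1275 × 45² = 449.4. SE = √(992.1/83) = 3.46, z = 1.84, power 45%.
- v = 80: variances 191.25 + 0.1275 × 17.5² = 230.3 and 191.25 + 0.1275 × 10² = 204.0. SE = √(434.3/83) = 2.29, z = 2.79, power 80%.

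| Failure score v | Expected difference | Pooled SD | Power |
|---|---|---|---|
| 45 | 6.4 | 22.3 | 45% |
| 55 | 6.4 | 19.6 | 55% |
| 70 | 6.4 | 16.3 | 71% |
| 80 | 6.4 | 14.7 | 80% |

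With equal loss and no true effect, the rejection rate stays at 5%.

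**Unequal loss, no true effect.** Assume 20% missing in the training arm and 10% in control. Bias = (0.20 − 0.10)(v − 90).
- v = 45: bias −4.5, SE 3.27, rejection rate 28%.
- v = 80: bias −1.0, SE 2.22, rejection rate 7%.

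The bias is against training, so nearly all the excess rejections would be false findings of harm. Reversing the imbalance reverses the sign and would favour training. With a milder split of 17% against 13%, the rejection rate is 8.5% (v = 45) to 5.4% (v = 80).

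**Cross-check.** A simulation of 4,000 trials per scenario with a control mean of 92.5 and 15% loss per arm gave power of 42%, 53%, 69% and 81% for v = 45, 55, 70 and 85, and 84% on available data. The pattern does not hinge on the assumed control mean.

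**Worst rank under Mann-Whitney.** Ranking all missing children as tied lowest needs no score. In simulation, 15% loss per arm gave power of about 60% and type I error of about 5%. Loss of 20% against 10% with no effect gave a rejection rate of about 20%.

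**The case against.** Several objections have force.

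- A reader might infer that the rule cannot be run at all. The protocol allows Mann-Whitney, and a tied worst rank would run without a score. But it does not say that worst rank is meant, it names the t test first, and worst rank has its own cost in power.
- A reader might infer that the maximum bias hypothesis contradicts the failure rule, since such fills often penalize the arms in opposite directions. The protocol does not define the term, and treating both arms alike may be what the authors mean by it. What stands is that the two statements are not reconciled.
- A reader might infer that more children will be lost from the training arm, pointing to the low training compliance in earlier studies reported under Hypothesis. That figure concerns adherence to training. A child who trained little can still be tested at 18 months. Unequal loss is plausible in an open-label trial where only one arm trains, but no passage gives loss by arm.
- A reader might infer that the rule always inflates the SD and the false-positive rate. At a failure score of 80 the pooled SD is 14.7, below 15, and power is at the planned 80%. With equal loss there is no type I inflation.
- The wording about not meeting the measurements is loose and could be read as a poor result. The heading and the two additional analyses show that a missing VSI is meant.
- Available-case analysis and multiple imputation are already planned. That is true, so the defect lies in their rank below an undefined rule.

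**Conclusion.** The point holds. The protocol fixes a binary-endpoint rule as the main handling of a missing continuous outcome, without the score, rank or cut-off needed to apply it, and leaves a second undefined rule beside it.

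At the planned 15% loss per arm, the expected effect falls from 7.5 to 6.4 points whatever score is assigned. Power lies between 45% and 80% for failure scores from 45 to 80, against about 84% on available cases. If loss were 20% in training and 10% in control with no true effect, the bias would be −4.5 to −1.0 points and the test would reject in 28% to 7% of trials; the opposite imbalance would favour training.

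The failure scores, the control mean and the unequal loss shares are all assumptions. The firm conclusion is that the primary result depends on a number that the plan does not contain. Since it governs the primary analysis, it should be settled before any outcome data are analyzed.

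**What to change.** 1. Delete the failure rule for the VSI.
2. Make the multiple imputation already listed the primary handling, with the WPPSI-IV indices from the EPIPAGE 2 assessment and from the intermediate visit in the imputation model. A likelihood-based repeated-measures model on the same data would serve equally well.
3. Keep the available-case analysis as a sensitivity analysis.
4. Replace the maximum bias hypothesis with one pre-specified delta-adjusted or worst-case sensitivity analysis, with its values stated, so that the sections on missing data and on patient selection agree.

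The cost is a change of wording and a little more analysis work. The indices are already part of the planned assessments, so no patients or visits are added.

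### Children without an 18-month VSI are to count as failed, but VSI is a continuous score and no failure value, rank or threshold is defined

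*Protocol article*

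**What the plan says.** All from the Protocol article.

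- **Endpoint** (Primary endpoint): VSI of the WPPSI-IV, built from two subtests. "The average score is 100 with a standard deviation of 15".
- **Comparison** (Analysis of primary endpoint): "The mean scores of the VSI will be compared between groups (Student t test or Mann Whitney test"). "The unadjusted analysis will be the primary analysis, and the adjusted analysis will be secondary analysis".
- **Missing data** (Methodology to account for missing data): the main rule is that "Children not meeting the primary endpoint measurements will be considered as having failed in the study regardless of their randomization group". Two further approaches are listed only as additional analyses: "Available data and,After multiple imputation of missing data".
- **Analysis population** (Patient selection to include in the analysis): every randomised child is included, by intention to treat. A maximum-bias hypothesis is invoked if necessary and not explained.
- **Sample size**: "80% power to detect a difference of 7.5 points on the VSI index (estimated standard deviation: 15) at 18 months", and "assuming that a potential 15% of patients will be lost to follow-up between baseline and last assessments", giving 83 per group.

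The failure sentence stands under the missing-data heading, so I read it as covering children who lack the 18-month VSI.

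**The concern.** Counting a missing child as a failure is a rule for a yes/no endpoint. VSI has no yes/no form here: the protocol defines no success, responder threshold, failure score or worst rank. All randomised children stay in the analysis, so a child without a VSI cannot simply be left out. A t test needs a number for that child, and a Mann-Whitney test needs a rank. Neither is given, and the choice between the two tests is also open.

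The two methods that suit a continuous score are placed second. Someone must therefore settle the value or rank later, possibly with the data in view. The primary p-value can then depend on that choice and on how losses fall between the arms. Unequal loss is plausible: the trial is open-label, and only the Cogmed arm has the training sessions and weekly parent interviews. Applying the rule to both arms alike does not protect against this.

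**Working it through.** **Inputs from the protocol:** 83 per arm, SD 15, difference 7.5, significance level 0.05 (taken as two-sided), loss 15%.

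**Assumptions not in the protocol:** control mean 90; loss unrelated to VSI; failure score F from 45 to 90; a 10%/20% split as an example of unequal loss.

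**The plan's own figure.** A 7.5-point difference with SD 15 is 0.5 SD, which needs 64 completers per arm for 80% power by t test. Then 64/0.85 = 75.3, so 76 per arm or 152 in total, not 166. The stated number errs on the high side: 83 × 0.85 ≈ 70 completers per arm give about 84% power on available data. That 84% is the benchmark below.

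**Formulas.** For an arm with true mean m and loss p, with missing children set to F:

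- mean = (1 − p)m + pF
- variance = (1 − p) × 225 + p(1 − p)(m − F)²
- SE of the difference = √[(sum of the two variances)/83]
- power ≈ Φ(difference/SE − 1.96)

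**Balanced 15% loss, true difference 7.5 (means 90 and 97.5).** F cancels from the difference: 0.85 × 7.5 = 6.4 at every score. The score acts only through the variance, 191.25 + 0.1275(m − F)².

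| F | Variance, control | Variance, Cogmed | SE | Power |
|---|---|---|---|---|
| 45 | 449.4 | 542.7 | 3.46 | 45% |
| 55 | 347.4 | 421.5 | 3.04 | 55% |
| 70 | 242.2 | 287.7 | 2.53 | 71% |
| 80 | 204.0 | 230.3 | 2.29 | 80% |
| 85 | 194.4 | 211.2 | 2.21 | 82% |
| 90 | 191.2 | 198.4 | 2.17 | 84% |

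Simulation (20,000 trials per scenario, each child lost at random) agrees to within about one percentage point. With no true effect and balanced loss, the false-positive rate stays at about 5% at every F.

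**No true effect, 10% loss in one arm and 20% in the other (both means 90).** The bias is (0.20 − 0.10)(90 − F), against the arm with more losses. The variances are 202.5 + 0.09(90 − F)² and 180 + 0.16(90 − F)².

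| F | Bias, points | SE | False positives (two-sided) |
|---|---|---|---|
| 45 | 4.5 | 3.27 | 28% |
| 55 | 3.5 | 2.88 | 22–23% |
| 70 | 2.0 | 2.41 | 13% |
| 85 | 0.5 | 2.16 | 5.6% |
| 90 | 0 | 2.15 | 5% |

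**True difference 7.5, 20% loss on Cogmed and 10% on control.** Expected difference = (0.8 × 97.5 + 0.2F) − (0.9 × 90 + 0.1F) = 0.1F − 3. That is 4.0, 2.5 and 1.5 points at F = 70, 55 and 45, with power of about 35%, 13% and 7%.

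**Mann-Whitney with missing children ranked last (simulated).** Power is about 60% with balanced 15% loss. False positives are about 20% with the 10%/20% split.

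**Sensitivity to the loss model.** Fixing the number lost instead of drawing it at random gives power of 75%, 57% and 43% at F = 70, 55 and 45 with balanced loss. It gives false positives of about 12%, 19% and 24% with the 10%/20% split. The pattern is the same.

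**The case against.** **The analysis is not impossible.** A reader might infer that no primary analysis can be run at all. That goes too far. The protocol permits a Mann-Whitney test, which can place failures below every observed score without a number. But the protocol neither states this ranking nor fixes which test applies, and worst ranks carry the power loss and false-positive rate shown above. The rule is undefined; it is not unworkable on every reading.

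**The score does not always drive the result.** A reader might also infer that whatever score is chosen largely decides the trial. With balanced loss it does not: the expected difference is 6.4 at any score, false positives are not inflated, and power is about 79% to 84% at scores of 80 to 90. The serious distortion needs a clearly low score, and for bias it also needs unequal loss. The protocol gives only an overall 15%, so a 10%/20% split is hypothetical, if plausible.

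**The sample size section is not in contradiction.** Inflating for 15% loss is routine and does not say how lost children are analysed. The 166 also exceeds what its inputs require. I do not count this as an inconsistency.

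**A fuller document might define the value or rank.** It might, and a condensed article need not carry every detail. But this article does state its main missing-data rule, and that rule does not fit its endpoint. The maximum-bias sentence does not help, since it is also undefined. If it means opposite assignments by arm, it conflicts with a rule that ignores the arm.

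**Conclusion.** The point holds, and the rule should be changed before analysis. The primary missing-data rule has no meaning for a continuous VSI until a value or rank is added, and none is stated.

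The size is conditional. Any failure score shrinks a true 7.5-point difference by 15% under balanced 15% loss. Power falls below the stated 80% when the score is clearly below the sample mean: about 70% at 70, 55% at 55, 45% at 45, and about 60% under worst ranks. If losses also differ between arms and the score is low, the comparison is biased toward the arm with fewer losses, and false positives rise to between 13% and 28% in the 10%/20% example. At scores of 85 to 90 the false-positive rate stays near 5%, though values so close to the assumed control mean hardly express failure.

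These figures rest on the assumed control mean of 90, the chosen scores, the example split and loss unrelated to VSI. The absence of a failure value or rank rests on the text alone.

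**What to change.** - **Primary handling.** Delete the failure rule for VSI. Make the multiple imputation already listed, or an equivalent likelihood-based analysis, the primary handling of missing 18-month VSI.
- **Imputation model.** Impute within arm from baseline VSI, inclusion WMI, 8-month VSI and WMI, centre and twin status. The 8-month visit already collects "IQ and its main indices (WPSSI IV"), which include both indices. With 18 centres and 83 children per arm (83/18 ≈ 4.6 per centre), centre will probably need pooling or a random effect.
- **Baseline VSI.** The Primary endpoint section says VSI is measured at inclusion, but the inclusion visit lists only WMI from the WPPSI-IV. Reconcile the two and state the source of baseline VSI.
- **Supporting analyses.** Keep available data as supportive. Add a delta-adjusted analysis that lowers imputed values by stated amounts, separately in each arm.
- **Failure or worst-rank analysis.** If wanted, keep it as a sensitivity analysis only, with its value or rank and its test fixed in advance. Define the maximum-bias wording or remove it.

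The cost is a wording change in the protocol and analysis plan. No new data are needed, provided baseline VSI is in fact recorded. The primary result would then rest on a missing-at-random assumption, and the delta-adjusted analysis shows how far the conclusion depends on it.
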